### Materials

Primary outcomes are assessed through the parent SCED data collection, while the secondary outcomes are assessed through child SCEDs, pre/post-measures and the child’s medical records.

Primary outcomes.

Child behavior problems.Parental self-efficacy.Parental stress.

Secondary outcomes.

Child mental health problems.Parents’ mental health.Parents’ quality of life.Goal attainment and client satisfaction.Child medical data.Children’s positive and negative experiences of family life.

In the current study, data are collected from five sources:

Parent weekly short measures.Validated questionnaires at pre-, post- and 3-month follow-up (T1, T2, T3).Forms on goal, goal attainment and client satisfaction with the intervention.Data from the child’s medical records.Child weekly short measures.

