### Procedure

Parent weekly measures will be collected via telephone by research assistants, with responses entered into REDCap. Data collection spans 15, 18, or 21 weeks, depending on the participant’s baseline length (4, 7, or 10 weeks). Pre-, post-, and 3-month follow-up questionnaires will also be distributed via REDCap, with pre-measures sent before baseline and post-measures after the intervention. Goal setting, goal attainment, and client satisfaction forms will be sourced from the Everyday Life and Parenting materials.

Child health data will be obtained through the Uppsala Region’s procedure for accessing research data from the electronic medical record system Cosmic. Child weekly measures will be sent digitally via REDCap and completed during the same weeks as the parent measures.

Intervention fidelity will be assessed through a checklist completed by course leaders after each module, indicating which session elements were completed.

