### Reliable change

To obtain a picture of whether changes in intensity and frequency of child behavior problems (ECBI) are both reliable and clinically significant, we will classify children as recovered, improved, unchanged or deteriorated. This will be done by incorporating both a measure of whether the change in scores is larger than what is expected due to measurement error of the tool i.e., statistical significance (Reliable Change Index - RCI) as well as the participant’s shift from a clinical state to a non-clinical state i.e., clinical significance (Clinically Significant Change– CSC) [54]. This is calculated for each individual based on pre- and post-data, and presented as percentages (percentage of children who were classified as recovered, improved, unchanged and deteriorated). We will also conduct sub-group analysis comparing girls and boys. Even though the sample will be too small for detecting small to medium effects in sub-group analyses, including such analyses will enable meta-analyses to do so.

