### Health economic evaluation

The health economic evaluation will be performed according to the Consolidated Health Economic Evaluation Reporting Standards 2022 Statement [57] and will include the following analyses: (1) a cost-effectiveness analysis using cost per improved case (based on the RCI/CSC) as the outcome, and (2) a series of cost-utility analyses using cost per quality adjusted life years (QALYs) gained for children (using SDQ scores mapped onto a multi-attribute utility instrument using available algorithms), for parents (using the scores from the AQOL-8D) and for the dyad as the outcome.

Costs will be analyzed from two different perspectives: a health care provider perspective and a societal perspective. The health care provider perspective includes the cost to run the intervention (e.g., therapist salary costs, administration) which will be collected from project documentation at the clinic. The societal perspective includes, in addition to intervention costs, other health care costs (health care utilization and medication), as well as costs beyond health care, including social support, and indirect costs related to lost productivity for parents (related to absence from paid and unpaid work) collected via the TIC-P.

Total costs and total QALYs will be aggregated over the trial period and estimated using the area under the curve method [58]. Differences in improved cases, total QALYs and total costs for children and parents before and after the intervention will be analyzed using regression models.

In the cost-effectiveness and cost-utility analyses, we will estimate an incremental cost-effectiveness ratio (ICER) as the ratio between the difference in costs and the difference in improved cases and QALYs for children, parents and the dyad between pre and post intervention for each costing perspective. Uncertainty around the cost and effect data will be explored using non-parametric bootstrapping and plotted on a cost effectiveness plane [59]. The probability of cost-effectiveness of the intervention at different values of willingness to pay will be estimated and represented visually as a cost-effectiveness acceptability curve [60].

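### The pre-versus-post ICER has no stated counterfactual: improved cases are zero at pre by construction, and the before/after difference in total QALYs is undefined without an added convention

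*Protocol article*

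**What the plan says.** All of this is in the protocol article.

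- **Health economic evaluation, effect unit:** "a cost-effectiveness analysis using cost per improved case (based on the RCI/CSC) as the outcome". Cost-utility analyses for children, parents and the dyad follow.
- **Health economic evaluation, accumulation:** "Total costs and total QALYs will be aggregated over the trial period and estimated using the area under the curve method".
- **Health economic evaluation, contrast:** "Differences in improved cases, total QALYs and total costs for children and parents before and after the intervention will be analyzed using regression models". The ICER is then defined as follows: "ratio between the difference in costs and the difference in improved cases and QALYs for children, parents and the dyad between pre and post intervention". It is computed under both costing perspectives, with bootstrapping, a cost-effectiveness plane and an acceptability curve.
- **Reliable change:** children are classed as recovered, improved, unchanged or deteriorated on the ECBI. "This is calculated for each individual based on pre- and post-data, and presented as percentages".
- **Materials:** the utility and resource-use instruments belong to the "Validated questionnaires at pre-, post- and 3-month follow-up (T1, T2, T3").
- **Procedure:** the questionnaires are distributed "with pre-measures sent before baseline and post-measures after the intervention", and the baseline lasts 4, 7 or 10 weeks.

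The Discussion concedes that the non-randomised single-case design cannot control time-related confounding such as maturation. The economic section names no comparator and does not repeat this caveat.

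**The concern.** An ICER needs two states that can each be costed and valued over the same length of time: what happened, and what would have happened otherwise. The article puts the pre-intervention state in the second role, and its own definitions do not fit that role.

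For improved cases, the pre value is a structural zero. For QALYs, a total needs elapsed time, and no measured interval lies wholly before the intervention. Left as it is, the analyst must choose a counterfactual after the data are in, and that choice can change the size and even the sign of the QALY difference. Bootstrapping describes sampling error only, so the acceptability curve would show an unstated assumption as if it were precision. Cost-effectiveness is in the article's title and is Objective 4, and the dissemination plan is aimed partly at policy makers.

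**Working it through.** The article states no ICER, cost, utility or improvement rate, so there is no planned figure to reproduce. The check sets the definitions side by side and then illustrates the consequences with assumed values.

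**1. Improved cases.** Reliable change defines the status from the pre and post scores jointly, so the number improved at pre is 0. The planned difference is N × p − 0 = N × p, where p is the proportion improved. The regression on improved cases before and after has no pre value that could vary. If a proportion b would have improved untreated, the additional cases are N × (p − b). Holding the cost difference fixed,

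factor on cost per case = p / (p − b).

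| p (assumed) | b (assumed) | Factor |
|---|---|---|
| 0.40 | 0.05 | 0.40/0.35 = 1.14 |
| 0.40 | 0.10 | 0.40/0.30 = 1.33 |
| 0.40 | 0.15 | 0.40/0.25 = 1.60 |
| 0.40 | 0.20 | 0.40/0.20 = 2.00 |
| 0.30 | 0.05 | 0.30/0.25 = 1.20 |
| 0.30 | 0.20 | 0.30/0.10 = 3.00 |

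**2. QALYs.** T1 falls before baseline, T2 after the intervention and T3 three months later. There is no questionnaire at the end of baseline. For participants with a 4-, 7- or 10-week baseline and an 8-week intervention, and taking T2 at the end of the intervention, T1–T2 lasts 12, 15 or 18 weeks. Of that, 4/12 = 33%, 7/15 = 47% or 10/18 = 56% is baseline. The planned area under the curve gives one total per person and no pre total to subtract.

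Assume utilities of 0.70, 0.75 and 0.75 at T1, T2 and T3, and 13 weeks from T2 to T3.

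- Area T1–T2 = 0.725 × weeks/52 = 0.1673, 0.2091 and 0.2510.
- Area T2–T3 = 0.75 × 13/52 = 0.1875.
- Later minus earlier interval = +0.0202, −0.0216 and −0.0635.
- Area above T1 carried forward = 0.025 × weeks/52 + 0.05 × 13/52 = +0.0183, +0.0197 and +0.0212.

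The same health gain changes sign in the interval contrast only because the intervals differ in length. The carry-forward contrast is stable, but it credits all change to the intervention. If half the utility gain were natural, it would halve to +0.0091, +0.0099 and +0.0106. If untreated utility would instead have fallen by half as much (0.025), it would be 1.5 times as large: +0.0274, +0.0296 and +0.0317.

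**3. Horizon.** Costs and QALYs are totalled over a trial period that is not defined and may run to T3. The improved status uses pre and post scores, hence T2. If the period does run to T3, the cost per improved case has about three more months in its numerator than in its denominator. If it stops at T2, the two agree.

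**The case against.** The strongest reply is that this is a condensed article of an openly uncontrolled study. The Discussion admits that time effects are not controlled and that this weakens the internal validity of the study. An interpolation or carry-forward rule could sit in a fuller plan. The root cause is the single-group design, which wording in the analysis section cannot cure. Much of this stands, and it limits the point in five ways.

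- A reader might infer that no QALY difference can be computed. That goes too far: holding T1 utility constant gives one from the planned data. What is missing is the convention. The interval contrast above is one available reading, not something the article specifies.
- A reader might take the horizon mismatch as established. The trial period is undefined, and a T1–T2 reading is open for both sides of the ratio.
- A reader might say that deteriorated children must be subtracted. The article chose cost per improved case, and netting off is a preference, not a correction.
- A reader might conclude that the bias always favours the intervention. With the cost difference held fixed, that is true of the gross count of improved cases if any child would have improved untreated. For QALYs it could go either way, since untreated utility might have fallen.
- Carrying T1 forward still credits all change to the intervention, so it cannot stand alone as the remedy.

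The reply does not remove the point itself. The article does not leave the contrast to another document. It states the before/after contrast twice, in terms that its own definition of improvement and its measurement schedule do not support. The general caveat in the Discussion changes neither the ICER nor the acceptability curve.

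**Conclusion.** The concern holds in this form: the ICER contrast is badly fixed. For improved cases it equals all improvers and assumes zero background improvement. For total QALYs it is undefined without an added convention. The common horizon is ambiguous.

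The size cannot be read from the documents. With 40% improved and 5–20% background improvement, the cost per additional improved case is 1.14 to 2.0 times the planned figure; with 30% improved it is 1.2 to 3.0 times. These factors rest on assumed rates and a fixed cost difference. The QALY figures rest on assumed utilities, a 13-week follow-up and T2 at the end of the intervention. The structural argument needs none of these assumptions.

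This should be fixed but does not threaten the primary analysis: cost-effectiveness is a secondary objective, and the primary outcomes come from the parents' weekly measures.

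**What to change.** In the Health economic evaluation section:

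1. State the counterfactual, for example T1 utility carried forward over the same duration as the observed curve. Treat the T1 cost rate in the same way if the TIC-P recall window, which the article does not give, allows it.
2. Define the incremental QALY as the area between the observed and the carried-forward curves.
3. Use one horizon for costs and effects, and name it. If it is T3, classify RCI/CSC at T3 as well and show T2 beside it.
4. Replace the difference in improved cases with the proportion improved. Add a sensitivity analysis over assumed background improvement, for example 0–20%, and one for QALYs with background change in either direction.
5. Label the ICER and acceptability curve as uncontrolled, versus baseline carried forward.
6. Report the proportion deteriorated alongside. Netting it off is optional.

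The cost is a revised paragraph and modest extra analysis on data already planned, with the TIC-P recall window to be confirmed. The results will usually span a wider and less favourable range.

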### Patient and public involvement

This project has been co-created together with clinical child health psychologists, a special education teacher, the last author (KF) and the first author (AD). The collaboration between the clinicians and the researchers will continue during the entire project and the clinicians will constitute the Clinical expert group. The researchers and Clinical expert group have monthly meetings. This group has actively participated in the preparation phase of the project, and they are involved in delivering the intervention. Furthermore, they will be invited to interpret the results. However, they will not be collecting data, nor analyzing it, in order to minimize the risk for bias.

In addition to this, we formed Parent Council consisting of four parents of children with subclinical NDDs. The main task of the council was to advise the team on finalizing the design of the project before the ethical application was due in June 2024. They specifically worked on issues of appropriateness and communication with the target group. Examples of specific tasks performed were co-creating advertisement for the project, writing information material and advice on recruitment. They were also asked for feedback on the measurements. Thus, the Parent council has been vital for the project.

### Ethical considerations

The study was granted Ethical approval by the Swedish Ethical Review Authority (2024-03064-01) and will be performed in accordance with the Declaration of Helsinki. Information about the study (aimed at parent and child respectively) will be provided. Informed written consent will be obtained from parents participating in the study. If the child has two guardians, the consent of both is needed for the child to participate in the study. The informed consent includes written information about the study and information about the possibility for participants to withdraw from the study at any time. The template provided by the Swedish Ethical Review Board will be used for the informed consent. Parents or legal guardians of all participating children will give their written informed consent on behalf of their children, prior to inclusion in the study. The children will be asked for their assent before answering the weekly short measures.

Participants will be compensated with vouchers for their involvement in this study. Research publications and data dissemination will not include identifiable data. Swedish General Data Protection Regulation will apply to all aspects of the study.

We have a three-fold communication strategy to disseminate the findings. The first part is aimed at professional community and policy makers on both national and regional levels. The research group and the clinical project group have well established contacts with interested parties both locally, regionally and nationally. We regularly participate and are invited to present at conferences and meetings with municipalities, regions and other bodies.

The second part is aimed at the interested public which can be reached through national patient/interest organizations, social media and traditional media. The third part is to disseminate the findings in the scientific community through publishing the results in suitable scientific journals and presenting them at national and international conferences.

## Discussion

This paper outlines the protocol for the evaluation of the Everyday Life and Parenting group parenting intervention for parents of children aged 2–6 years with subclinical NDDs and mental health problems. Some strengths and limitations of this have been recognized. Firstly, by collecting and evaluating longitudinal data from children and/or their parents, the study will provide valuable insights into the trajectories of mental health and well-being in this group. Secondly, the study will involve pre-school children as informants, providing crucial information about their experiences and perspectives on family life. Thirdly, the use of pre-, post- and follow-up questionnaires will allow reliable and clinically significant changes to be assessed in child emotional and behavioral problems, parental self-efficacy, stress, and behavior.

Despite these strengths, the use of SCED without randomization presents a methodological limitation, as it prevents control for potential confounding variables related to time, such as historical events or maturational effects in children. While this design limitation affects the internal validity of the study, the strengths of this research have the potential to make a significant contribution to understanding the effectiveness of an early parenting support group intervention specifically designed for children with subclinical NDDs. This includes reducing child EBP and parental stress, and improving parental self-efficacy, well-being, and quality of life. The study will also assess the cost-effectiveness of the intervention.

## Data Availability

No datasets were generated or analysed during the current study.

## Abbreviations

ABA: Applied Behavior Analysis
ADHD: Attention Deficit Hyperactivity Disorder
AQOL-8D: Assessing Quality of Life 8 Dimensions
ASD: Autism Spectrum Disorder
CSC: Clinically Significant Change
EBP: Emotional and Behavioral Problems
ECBI: Eyberg Child Behavior Inventory
GHQ-12: General Health Questionnaire
ICER: Incremental Cost-Effectiveness Ratio
ICF: The International Classification of Functioning
MaaP: Me as a Parent
NAP: Nonoverlap of All Pairs
NDD: Neurodevelopmental Disorder
PSS: Parental Stress Scale
QALY: Quality Adjusted Life Years
RCI: Reliable Change Index
REDCap: Research Electronic Data Capture
SCED: Single Case Experimental Design
SDQ: Strengths and Difficulties
TIC-P: Trimbos/iMTA questionnaire for costs associated with Psychiatric Illness
